## Abstract

**Background:**

Little research has examined whether alcohol reduction interventions improve antiretroviral therapy (ART) adherence and HIV treatment outcomes. This study assesses the efficacy of an intervention for reducing alcohol use among HIV patients on ART who are hazardous/harmful drinkers. Specific aims include adapting a blended Motivational Interviewing (MI) and Problem Solving Therapy (PST) intervention for use with HIV patients; evaluating the efficacy of the intervention for reducing alcohol consumption; and assessing counsellors’ and participants’ perceptions of the intervention.

**Methods/Design:**

A randomised controlled trial will evaluate the intervention among ART patients in public hospital-based HIV clinics in Tshwane, South Africa. We will recruit patients who are HIV-positive, on ART for at least 3 months, and classified as harmful/hazardous drinkers using the AUDIT-3. Eligible patients will be randomly assigned to one of three conditions. Patients in the experimental group will receive the MI-PST intervention to reduce harmful/hazardous alcohol use. Patients in the equal-attention wellness intervention group will receive an intervention focused on addressing health risk behaviours. Patients in the control condition will receive treatment as usual. Participants will complete an interviewer-administered questionnaire at baseline and 3, 6 and 12 months post-randomisation to assess alcohol consumption, ART adherence, physical and mental health. We will also collect biological specimens to test for recent alcohol consumption, CD4 counts and HIV RNA viral loads. The primary outcome will be reduction in the volume of alcohol consumed. Secondary outcomes include reduction in harmful/hazardous use of alcohol, reduction in biological markers of drinking, increase in adherence rates, reductions in viral loads, and increases in CD4 T-cell counts. A process evaluation will ascertain counsellors’ and participants’ perceptions of the acceptability and effectiveness of the interventions.

**Discussion:**

We have obtained ethical approval and approval from the study sites and regional and provincial health departments. The study has implications for clinicians, researchers and policy makers as it will provide efficacy data on how to reduce harmful/hazardous alcohol consumption among HIV patients and will shed light on whether reducing alcohol consumption impacts on HIV treatment adherence and other outcomes.

**Trial registration:**

Pan African Clinical Trials Register Number: PACTR201405000815100.

**Electronic supplementary material:**

The online version of this article (doi:10.1186/1471-2334-14-500) contains supplementary material, which is available to authorized users.

## Background

The consumption of alcohol has been closely investigated within the context of HIV [1]. Data suggests that hazardous alcohol use directly contributes to the acquisition and transmission of HIV as well as to antiretroviral therapy (ART) non-adherence, the worsening of HIV disease, progression to AIDS, and mortality [2–4]. Not only does South Africa have high numbers of persons who are HIV positive and on ART, but it also has one of the highest levels of per capita alcohol consumption *per drinker* globally and one of the highest levels of heavy episodic drinking globally among men and women [5].

ART is essential for improving and maintaining physical health, reducing HIV viral load, and reducing morbidity and mortality among people living with HIV and AIDS (PLWHA) [6]. Sub-optimal adherence to ART regimens can result in the development of resistance to ART, and ultimately poorer treatment outcomes, and mortality [7–10]. Alcohol consumption is a concern in relation to ART as alcohol may impact the cognitive processes necessary to maintain adequate adherence [11]. Furthermore, beliefs that ART medications should not be taken while consuming alcohol may cause drinkers to fail to adhere to treatment [12–15]. Hendershot et al.’s meta-analysis found that drinkers were 50%-60% as likely to be adherent as non-drinkers [16]. This effect was amplified for problem drinkers, who were only 47% as likely to be adherent as non-problem drinkers or abstainers. In addition, missed ART doses occur primarily on drinking days [17]. In keeping with these findings, the consumption of alcohol has been shown to be significantly associated with time to ART treatment failure as well as subsequent survival [18].

At a molecular level, in vitro experiments have demonstrated that exposure to even a moderate dose of alcohol can increase HIV replication in peripheral blood mononuclear cells [19]. Evidence suggests that alcohol use may lead to an increase in HIV viral replication in those infected with HIV [19–23]. Alcohol consumption may also impact CD4 cells, with research demonstrating lower CD4 counts among heavy alcohol users [24–26].

Despite the demonstrated links between alcohol consumption and HIV, few randomised controlled trials (RCTs) have evaluated the efficacy of alcohol-focused interventions in the context of HIV treatment. Furthermore, when such interventions have been implemented, the results have been equivocal [27–30]. There is considerable evidence from systematic reviews of RCTs that brief interventions (BI) are effective for reducing the volume of alcohol consumed and hazardous/harmful alcohol use among a range of patient populations, including those receiving primary health care [31–33]. The brief interventions (BI) we have chosen are based on motivational interviewing (MI) techniques and problem-solving therapy (PST), a variant of cognitive-behavioural therapy (CBT). Both of these modalities have proven efficacy for reducing alcohol consumption and problem drinking among a range of patient populations [34–38]. In the proposed study, we will bolster the effect of MI on hazardous and harmful drinking and improve the durability of MI’s effects by blending MI techniques with core elements of PST. Similar to MI, there is a large body of evidence in support of the efficacy of CBT for reducing problem drinking [38–41]. While the elements of this blended intervention are based on well-established treatment modalities of proven efficacy, they have not been implemented among PLWHA in South Africa. However, findings from our earlier work suggest that this blended intervention is likely to be acceptable to this population [42].

The overall goal of this project is to improve knowledge on the efficacy of an alcohol reduction intervention on alcohol consumption among PLWHA on ART, ART adherence and HIV treatment outcomes. The study has the following specific aims:(i)*To adapt a blended MI and PST intervention to address harmful/hazardous alcohol use in HIV positive populations in Tshwane, South Africa*.(ii)*To assess the efficacy of the blended MI-PST alcohol-focused intervention for reducing the average volume of alcohol consumed, improving ART adherence, maintaining ART adherence, improving HIV treatment continuation, and reducing disease progression relative to an equal-attention wellness intervention and treatment as usual (TAU) control group*. We hypothesise that those patients who receive the MI-PST alcohol-focused intervention will be more likely than those in the wellness intervention or TAU control groups to reduce their volume of alcohol consumption (our primary outcome) and that the participants in the alcohol-reduction intervention who reduce their alcohol consumption will have significantly greater improvements in their degree of ART adherence and in their HIV disease-related outcomes (including their treatment continuation and the progression of their disease) relative to participants in the wellness intervention or control group.(iii)*To qualitatively assess counsellors’ and participants’ subjective responses to the blended MI-PST intervention*.

## Methods/Design

The proposed project will comprise three phases corresponding to the three specific aims. In Phase 1 (Aim 1), we will adapt an existing blended MI-PST intervention for use among patients receiving treatment for HIV. Phase 2 (Aim 2) will entail an RCT to assess the efficacy of this blended intervention in reducing alcohol consumption and in turn, improving levels of adherence to ART and HIV disease outcomes among ART patients in clinical care. Phase 3 (Aim 3) will involve a process evaluation to assess the counsellors’ and participants’ perceptions of the acceptability and impact of the alcohol intervention.

### Phase one: adapting MI-PST to reduce alcohol use among PLWHA initiating ART

We will adapt and refine our MI-PST intervention materials for use among patients receiving HIV disease care through conducting four focus group discussions (FGDs) with up to eight patients per group. They will discuss their perceptions about (1) how alcohol use relates to ART adherence; (2) potential barriers and facilitators to patient uptake of the proposed interventions; and (3) the acceptability, appropriateness and relevance of the proposed interventions. Each group discussion will be audio-taped and transcribed. Participants will receive refreshments during the FGDs, an incentive (a supermarket voucher worth ZAR50, approximately US$4.76), and ZAR50 for public transport to the clinics.

Once the intervention has been initially adapted, we will train health counsellors to pilot the blended MI-PST intervention for alcohol use and the MI-PST intervention for the wellness intervention. This pilot will assess the feasibility and acceptability of conducting these interventions among PLWHA in clinical care settings and test the intervention materials and procedures prior to scaling up for the RCT. Up to 20 patients who meet the eligibility criteria will be requested to provide informed consent prior to assessment and participation in the intervention. During the assessment, we will pre-test the study’s battery of questions to get a sense of how long it would take to complete the assessment as well as whether there is a need to revise any parts of the questionnaire.

In addition, we will pre-test the procedures for collection of biological specimens from the participants in order to assess their HIV viral load and CD4 T-cell counts, and Phosphatidylethanol (PEth), a biomarker indicative of recent alcohol use. Participants will then receive either the 4 session blended MI-PST alcohol reduction or the equal attention MI-PST wellness intervention over two days (Sessions 1 and 2 in Day 1, and Sessions 3 and 4 in Day 2).

Following the final intervention session, they will be re-interviewed to assess their perceptions of the factors that helped and hindered behaviour change. These interviews will be audio-taped and transcribed and used to further refine the intervention materials prior to their use in the RCT. Participants will receive an incentive after completing each intervention session and for completing the follow-up interview. Equal effort will be put into developing and adapting the alcohol and wellness interventions.

### Phase two: randomised controlled trial

#### Design

The proposed parallel, individual RCT will use a repeated measures design (see Figure 1, Consort diagram). The study will be a three-arm comparison, with one pre-intervention observation and three repeated measures post-intervention observations per participant. Randomisation to interventions will be done within sites.

**Figure 1 Fig1:**
[figure not shown]
**Consort diagram of the study design.**

#### Study population and sample size considerations

All participants will be recruited from ART clinics in hospitals in the Tshwane Health District. The inclusion criteria for the clinics include having funds for the duration of the project so that ART supplies do not run out, being located within the Tshwane Health District, and having a large active caseload of PLWHA receiving ART (e.g. at least 100 per week) to facilitate patient recruitment. Individuals will be eligible to participate in this research if they (1) are HIV-positive; (2) have taken ART for at least three months; (3) are not currently receiving treatment for TB (or latent TB infection); (4) are 18 years or older; (5) are classified as “harmful/hazardous drinkers” (have six (or four, if female) or more drinks on one occasion at least weekly, and score no more than 22 on the AUDIT); (6) are resident in the Tshwane Metropolitan Municipality or the general area served by the clinic/site; (7) have no substantial cognitive impairment; (8) are not currently enrolled in another trial; and (9) do not have extremely poor general health/functional status (Karnofsky clinical score > 50).

Sample size estimates are based on the numbers of patients needed to detect differences between intervention and control groups in the mean number of drinks per day (past 30/60 days) at 3, 6, and 12 months post randomisation, our main outcome measure. A study among HIV patients found that the mean number of drinks per drinking days was 3.58 (Standard Deviation (SD): 1.81) under an enhanced MI vs. 4.75 (SD: 3.22) under the control arm [43]. For two-sided testing at a significance level of 5% and power of 90%, with one pre- and three post- intervention measures with a within subject correlation of 0.7 between measurements, the required sample size using analysis of covariance methods is 260. Of the 260 participants, 130 will be allocated to the alcohol intervention and 65 to each of the wellness and TAU arms. This imbalance of sample sizes for the treatment combinations can cause loss of power of statistical tests of differences between the group outcomes (e.g. means). It may also produce sensitive results in small samples when the assumptions of equal variance between groups are violated. Nonetheless, our choice of the imbalanced design was based on valid scientific and practical reasons, as the intervention combination we plan to assess is of great interest. Thus, the higher sample size in the main intervention arm (alcohol intervention) was chosen as it is statistically more efficient to have more subjects in this group as we will be comparing its effect to each of the other two interventions. This sample size also allows adequate power (>90%) to detect a modest effect size (0.25) for the within-subjects component, and for a potential interaction between- and within-subjects factors. However, the actual number of participants needs to be inflated to take into account attrition over time. We estimate an overall attrition rate of 20% and therefore need to recruit 325 participants to take into account this attrition. Assuming four sites, this would create a site-specific sample size of 82 (66 after attrition).

We have no site-specific hypotheses, but if we want to include a safety margin for testing site specific effects of 0.30, we should allow for a site specific sample of 150 which would already include the attrition (120 per site before attrition). Of these, 75 would receive the alcohol intervention, and 38 each the wellness intervention and TAU. We will recruit participants from each site without an attempt to have equal numbers of men and women; we anticipate a ratio of about 2:1 females to males. Based on our prior data [44], we would estimate that about 40% of ART recipients will be alcohol drinkers. Of the alcohol drinkers, we estimate that about 15% would meet the criterion related to alcohol (have six (or four, if female) or more drinks on one occasion at least weekly, and score no more than 22 on the AUDIT). That research also suggests a participant eligibility rate of no more than 20%, so we would need to screen at least 750 patients at each site to reach our target sample of 150. Therefore we need to recruit participants from large facilities, suggesting that only hospital-based clinics would qualify as possible study sites. Thus, we plan to recruit participants from all four of the district hospitals in the Tshwane Health District, which cover a wide catchment area. The hospitals are: (1) Tshwane District Hospital, (2) Pretoria West Hospital, (3) Odi District Hospital, and (4) Jubilee Hospital. With four sites, our final sample size of 600 will include 300, 150 and 150 participants in the alcohol, wellness and TAU arms respectively. In the proposed district hospitals, there are HIV clinics in the form of separate outpatient departments (OPD). These HIV clinics carry very high volumes of patients, spanning the whole continuum of care.

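### The stated inputs do not give a required sample size of 260 at 90% power: they give 66 (two equal arms) or 116 (2:1:1), a conservative but untraceable figure

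*Protocol article*

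**What the plan says.** All of this is in the Protocol article, under Study population and sample size considerations.

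- **Effect and spread.** The mean number of drinks per drinking day in an earlier study "was 3.58 (Standard Deviation (SD): 1.81) under an enhanced MI vs. 4.75 (SD: 3.22) under the control arm".
- **Error rates.** "For two-sided testing at a significance level of 5% and power of 90"%.
- **Design.** "one pre- and three post- intervention measures with a within subject correlation of 0.7 between measurements".
- **Result.** "the required sample size using analysis of covariance methods is 260".
- **Allocation.** "130 will be allocated to the alcohol intervention and 65 to each of the wellness and TAU arms". The larger alcohol arm is justified because "we will be comparing its effect to each of the other two interventions".

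The 260 is inflated to 325 for 20% attrition, which is 82 per site, or 66 after attrition. The plan then adopts a larger sample as a safety margin for testing site-specific effects of 0.30: "a site specific sample of 150 which would already include the attrition (120 per site before attrition"). Four sites give the final 600, split 300/150/150.

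**The concern.** The paragraph supplies everything that a standard repeated-measures ANCOVA calculation needs, so a reader can check the result, and it does not check. The 260 and its 90% power are the article's only quantified power statement for the primary between-arm comparison. If they do not follow from the inputs, the reader cannot tell which assumptions were used. Nor does the article say what difference in drinking the final sample of 600 can detect. At stake is the traceability of the justification, not the number of patients.

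**Working it through.** **Inputs** (all from the sample size section): difference 4.75 − 3.58 = 1.17; SDs 1.81 and 3.22; two-sided 5% and 90% power, so (1.960 + 1.282)² = 10.507; r = 3 post measures, one baseline, ρ = 0.7. I use the normal approximation and equal correlation between all measurements.

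**ANCOVA variance factor** for the mean of the post measures, adjusted for baseline:

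(1 + (r − 1)ρ)/r − ρ² = (1 + 2 × 0.7)/3 − 0.49 = 0.80 − 0.49 = 0.31

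**Attempt to reproduce 260**

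- Two equal arms: n = 10.507 × (1.81² + 3.22²) × 0.31 / 1.17² = 32.5, so 33 per arm, **66 in total**.
- 2:1:1, alcohol against each smaller arm: n = 10.507 × (1.81²/2 + 3.22²) × 0.31 / 1.17² = 28.6, so 58/29/29, **116 in total**.

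Variants that keep ANCOVA with one pre and three post measures, for 2:1:1:

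| Variant | Total |
|---|---|
| Pooled SD 2.61 | 100 |
| SD 3.22 in both arms | 152 |
| Alpha 0.025 | 136 |
| 95% power | 144 |
| Alpha 0.025, 95% power and SD 3.22 in both arms | 216 |
| Stated SDs, alpha and power; any ρ from 0 to 0.9 | at most 164 |

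None reaches 260. Totals near 260 appear only when a stated input is dropped or changed:

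- ANCOVA at a single follow-up (factor 1 − 0.49 = 0.51), SD 3.22 in both arms, 2:1:1: 10.507 × 3.22² × 1.5 × 0.51 / 1.17² = 60.9, so 61 per smaller arm, 244 in total.
- Mean of three post measures without baseline adjustment (factor 0.80), SD 3.22 in both arms, two equal groups: 10.507 × 2 × 3.22² × 0.80 / 1.17² = 127.3, so 128 per group, 256 in total.
- Single-measure comparison of two equal arms at 95% power: 260.

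**Power of 130 against 65 with the stated inputs**

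- SE = √[0.31 × (1.81²/130 + 3.22²/65)] = 0.239; power = Φ(1.17/0.239 − 1.96) = **99.8%**.
- SD 3.22 in both arms: SE = 0.272; power = **99.0%**.

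**Steps after 260.** 260/0.8 = 325; 325/4 = 81.25, so 82; 82 × 0.8 = 65.6, so 66. These reproduce.

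**What the final 600 can detect.** 600 × 0.8 = 480 completers, 240/120/120.

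- With the plan's SDs: SE = √[0.31 × (1.81²/240 + 3.22²/120)] = 0.176; 90% power at 3.242 × 0.176 = **0.57 drinks**.
- With equal variances: SE = √[0.31 × (1/240 + 1/120)] = 0.0622 SD; 90% power at **0.20 SD**.

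The scale matters. With the plan's unequal SDs, an effect of 0.20 pooled SD (0.52 drinks) has 84% power.

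**Site margin.** 120/0.8 = 150. If 0.30 is Cohen's f for the three-arm between-subject test with ρ = 0.7, the noncentrality at 120 is 0.30² × 120 × m/(1 + (m − 1) × 0.7): 13.5 for m = 3 measures and 13.9 for m = 4. Power is then 91% and 92%.

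**The case against.** **The figure is harmless.** Under the stated inputs 260 is more than enough, and the number actually recruited is 600, set by a different argument. This stands, and it limits the point to a correction of text. It does not make the sentence right, because the article says that these inputs require 260 and they do not.

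**An article condenses the protocol.** That excuses omissions. Here the inputs are printed and the result attached to them is wrong.

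**A conservative ANCOVA reading comes close.** Because the section speaks of differences at 3, 6 and 12 months, a per-visit ANCOVA with the larger SD is conceivable. It gives 244, and 92% power for 130 against 65. This is a fair candidate, but it does not use the three post measures jointly and it replaces one of the stated SDs.

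**Stronger readings that the article does not support.**

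- A reader might infer that the pairwise comparisons are underpowered. If 260 came from the unadjusted calculation against pooled controls, 130 against 65 would have 76% power. That rests on one guessed origin among several, and the per-visit ANCOVA gives the opposite answer.
- A reader might call the 120 per site reversed. The phrase can mean before the attrition allowance is added, and 120/0.8 = 150 is correct. It is only awkward beside the 66 per site that the same section labels as after attrition.
- A reader might take 0.30 as a standardised mean difference and find 67% power with 60 against 30 completers. Cohen's f fits the stated 120 well and the mean-difference reading does not. The article also says that it has no site-specific hypotheses.

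**Conclusion.** The point holds as an arithmetic error. The stated inputs require 66 (two equal arms) or 116 (2:1:1), not 260, and 130 against 65 has about 99.8% power (99.0% with SD 3.22 in both arms), not 90%. The error is on the safe side and leaves no shortfall under the stated inputs. The later steps to 325, 82 and 66 are sound; only their starting number is unexplained, and its origin cannot be recovered from the article.

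The figures rest on the normal approximation, a common correlation of 0.7, and the smaller SD applying to the alcohol arm. Changing the SD assumption moves the 2:1:1 total between 100 and 152, which does not alter the conclusion. All figures are in drinks per drinking day, the scale of the cited means, whereas the section names drinks per day as the outcome.

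**What to change.** 1. Correct the required number and the power so that they match the stated inputs, or state the different inputs that give 260 (for example a single follow-up or a larger SD).
2. Give the detectable difference for the final 600 on the raw scale, with the SDs stated. With 480 completers (240/120/120) and the plan's SDs, this is about 0.57 drinks at 90% power in each pairwise comparison; about 0.20 SD applies only if variances are equal.
3. Rerun that calculation with inputs in drinks per day.
4. As wording only, describe the 120 per site as after attrition, to match the 66 per site. If 0.30 was meant as Cohen's f, say so and give its power (about 91–92% at 120 per site).

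The cost is text and one recalculation. No change to the number of patients follows.

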Given the repeated measures design, the main statistical analysis will involve repeated analysis of variance and analysis of covariance, using pre-treatment means and post-treatment means; or two-sample t-tests or chi-squared tests at the patient level data. The hypothesis that alcohol reduction will increase adherence will be tested via a repeated-measures Analysis of Variance (ANOVA). This will be an intent-to-treat (ITT) analysis. For our ITT analysis we will analyse our data based on the participants’ original allocation to the groups regardless of any subsequent group changes or participants’ degree of adherence to study protocols or their withdrawal from the study. We will assume data will be missing completely at random (MCAR) in order to enable imputation of missing data using standard techniques. We have postulated a main effect for the experimental condition without an interaction effect. In addition, we intend to use the CD4 T-cell counts and viral loads as objective biological endpoints, with the same statistical procedure being employed. Additional analyses will determine whether the pathway via reduction of alcohol consumption was indeed crucial to the differences in adherence. This can be measured by a cross-lagged panel design, where the alcohol in the time interval before the respective measurement of adherence will be assumed to have a significant effect. Structural equation modelling and path analysis will be used to test this assumption. Models will also be run with ART continuation as the endpoint. More advanced techniques, including generalised estimating equation and multilevel modelling, will also be employed. The association between the biomarker of alcohol consumption and self-reports of alcohol will be analysed using correlation and regression techniques with adjustments for possible confounders. The predictive ability of the biomarker will be assessed using sensitivity and specificity techniques to determine its ability to detect excessive self-reported consumption of alcohol.

#### Analyses for phase 3

Data analysis will be conducted using the same framework approach as described above for Phase 1. We will use the Phase 3 findings to assist with interpreting the findings of the RCT phase.

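### The 2:1:1 split is not more efficient for comparing the alcohol arm with each other arm, and the unequal-variance problem is not confined to small samples

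*Protocol article*

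**What the plan says.** All but the last item come from the protocol article, *Study population and sample size considerations*.

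- The allocation for the calculated sample is that "130 will be allocated to the alcohol intervention and 65 to each of the wellness and TAU arms". The final 600 keep the same ratio: 300, 150 and 150.
- The larger alcohol arm is justified as "statistically more efficient to have more subjects in this group as we will be comparing its effect to each of the other two interventions".
- The only SDs offered come from a cited study in HIV patients: "3.58 (Standard Deviation (SD): 1.81) under an enhanced MI vs. 4.75 (SD: 3.22) under the control arm". They are for drinks per drinking day.
- Just before the efficiency claim, the section concedes that the imbalance may cost power. It then says of unequal variance: "It may also produce sensitive results in small samples when the assumptions of equal variance between groups are violated". It also appeals to scientific and practical reasons for the imbalance.
- Under *Analyses for phase 2*, the main analysis "will involve repeated analysis of variance and analysis of covariance, using pre-treatment means and post-treatment means; or two-sample t-tests or chi-squared tests". Generalised estimating equations and multilevel models are named only as further techniques.

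**The concern.** The efficiency sentence is a statistical statement that can be checked, and the check goes against it. A shared arm can usefully be somewhat larger than the arms it is compared with, but doubling it overshoots. The quoted SDs make matters worse, because the extra patients go to the arm with the smaller SD.

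The second point concerns calibration. When the larger group has the smaller variance, a pooled variance leans towards that smaller variance and the standard error comes out too small. The size of this error depends on the allocation ratio and the SDs, not on N. A reader of the small-sample remark could conclude that 600 patients put the matter to rest. If the SDs are as quoted, they do not, and the confidence intervals for the primary comparison would be too narrow.

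**Working it through.** **Inputs.** SDs 1.81 (intervention) and 3.22 (control), variances 3.2761 and 10.3684; means 3.58 and 4.75, difference 1.17; correlation 0.7, one pre and three post measures; two-sided 5%, 90% power; total 260 as 130:65:65, final 600 as 300:150:150. All are from *Study population and sample size considerations*. The wellness SD is not given. I take it as 3.22 and vary it in step 5.

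**1. The plan's own figures.** 260/0.8 = 325 reproduces. The 260 does not. The ANCOVA factor is (1 + 2×0.7)/3 − 0.7² = 0.31, and (1.960 + 1.282)²/1.17² × 0.31 = 2.38.

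- Equal arms: 2.38 × (3.2761 + 10.3684) = 32.5, so 33 per arm, i.e. 66 for two arms or 99 for three.
- 2:1:1: 2.38 × (3.2761/2 + 10.3684) = 28.6, so 29 per comparator and 116 in all.

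Nothing below depends on 260. Only the ratio and the SDs matter.

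**2. Alcohol v one comparator.** Variance × N = s₁²/p₁ + s₂²/p₂, where p is the share of patients in the arm.

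| | 2:1:1 | 1:1:1 | Ratio |
|---|---|---|---|
| Equal SDs (=1) | 1/0.5 + 1/0.25 = 6 | 3 + 3 = 6 | 1.00 |
| Quoted SDs | 3.2761/0.5 + 10.3684/0.25 = 48.03 | 3 × 13.6445 = 40.93 | 1.173 |

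With equal SDs the best ratio is √2:1:1, which gives 5.83, about 3% below 6. With the quoted SDs the best ratio is √2 × 1.81/3.22, about 0.79:1:1, a smaller alcohol arm. At those SDs, 600 patients at 2:1:1 give the pairwise precision of 600/1.173 = 511 at 1:1:1.

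**3. Alcohol v both comparators combined.**

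- Equal SDs: 1/0.5 + 1/0.5 = 4 under 2:1:1, and 3 + 1.5 = 4.5 under 1:1:1. 2:1:1 has 11% lower variance.
- Quoted SDs: 2 × 13.6445 = 27.29 against 3 × 3.2761 + 1.5 × 10.3684 = 25.38. 2:1:1 is 7.5% worse.

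**4. Pooled standard error at 300 v 150, quoted SDs.** True variance: 3.2761/300 + 10.3684/150 = 0.0800.

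- Two-arm pooled variance: (299×3.2761 + 149×10.3684)/448 = 5.63. Times (1/300 + 1/150) this is 0.0563. SE ratio √(0.0563/0.0800) = 0.84.
- Three-arm mean square error: (299×3.2761 + 298×10.3684)/597 = 6.82, giving 0.0682. SE ratio 0.92.

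Coverage of a nominal 95% interval is 2Φ(1.96 × ratio) − 1: 90.0% and 93.0%. The corresponding rejection rates if the means were equal are 10.0% and about 7.0%. At N = 260 and 480 they are the same to within 0.1 of a percentage point.

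Simulation at 300:150:150 (8,000 runs, equal means, quoted SDs) gave rejection rates of 9.4% for the pooled t-test, 10.2% for two-arm ANCOVA, 6.9% for the three-arm ANCOVA contrast and 4.6% for Welch.

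**5. Wellness SD.** If it were 1.81, the alcohol v TAU figures in step 2 and the two-arm figure in step 4 would stand, since they do not use it. The three-arm contrast of alcohol v TAU would move from about 7% to 12.0% rejection (88% coverage). For alcohol v wellness the two SDs would then be equal, and 2:1:1 would merely tie with 1:1:1.

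**The case against.** **The tests may not assume equal variances.** The protocol does not say the t-test is pooled, and Welch would hold about 5%. It also lists generalised estimating equations, and an analysis plan that is not shown may settle the variance estimator. This stands for the t-test. It does not remove the point: ANOVA and ANCOVA in their usual form assume a common residual variance and are named as main analyses, and the protocol itself ties the concern to small samples.

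**Type I error.** A reader might infer that the primary test runs at 7–10%. The documents do not support that without a condition. Those rates need equal means together with SDs of 1.81 and 3.22. The quoted SDs came with different means, so the smaller SD may itself be an effect of treatment. If the intervention changes nothing, randomised arms share one SD and the error is 5%. The coverage shortfall needs no null hypothesis; it applies in the plan's own scenario, where means and SDs both differ.

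**The principle is sound, and there is a contrast that gains.** A shared arm should be somewhat larger when SDs are equal, and against the combined controls 2:1:1 is better in that case. Both are true, but the stated reason is the comparison with each arm separately.

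**The cost is already admitted.** The section does concede possible loss of power. That concession contradicts the efficiency claim rather than correcting it. The small-sample sentence does not say outright that large samples are safe, but as worded it invites that reading.

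**Lost power.** A reader might also infer that the trial is underpowered. It is not on the stated inputs: ANCOVA power exceeds 99% under either split at 260. Even with no gain from baseline or repeated measures, 480 completers give about 96% (2:1:1) or 98% (1:1:1).

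**Conclusion.** The point holds in a limited form. For the comparison the protocol names, 2:1:1 has no precision advantage over 1:1:1 with equal SDs and about 17% more variance at the quoted SDs. That is an incorrect justification, not a threat to power. The restriction of the variance concern to small samples is also wrong: if SDs differ as quoted and a common variance is used, 95% intervals cover about 90% (two-arm pooling) or 93% (three-arm), whatever the sample size.

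These sizes are illustrative. They rest on SDs for drinks per drinking day from a cited study, whereas the sample-size section names drinks per day as the main outcome. For the wellness arm and the three-arm figures they also rest on an assumed SD of 3.22. That 6/N equals 6/N rests only on equal SDs.

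The material does not show that the allocation must change. With equal SDs, 1:1:1 gives up precision against the combined controls. At the quoted SDs it would not by itself calibrate a three-arm pooled contrast, which would reject at 3.4% instead of 5%.

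**What to change.** - *Analyses for phase 2*: state that the primary comparison does not assume equal variances. Use Welch for a t-test, heteroscedasticity-robust standard errors for ANCOVA, or arm-specific residual variances in a mixed model. This is valid whichever SDs occur.
- *Study population and sample size considerations*: delete the efficiency claim and the restriction to small samples. State instead that 2:1:1 is kept for practical reasons, that it brings no gain in precision over equal allocation for the comparison with each other arm, and that it loses precision if the SDs are as quoted.

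The cost is wording only. Sample size, allocation and trial conduct stay as they are.
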